## Abstract

**Background:**

The prevalence of sacroiliac joint pain (SIJP) is estimated to be 10–30% in patients with chronic low back pain. Numerous conservative and surgical treatment modalities for SIJP have been described with limited evidence regarding long-term pain relief.

Spinal cord stimulation (SCS) is a well-established technique to treat patients with chronic low back pain. However, the effect on patients with SIJP is not consistent. Therefore, peripheral nerve stimulation (PNS) for chronic SIJP was implemented in experimental trials. Clinical data on PNS for SIJP is still lacking. The authors present a case series and a protocol for a prospective, multicenter study to determine the effect of PNS in patients with chronic intractable SIJP.

**Method:**

A multicenter, prospective randomized controlled trial was designed. Patients with chronic intractable SIJP will be recruited and randomized in a 4:3 ratio to either the peripheral nerve stimulation group or to the best medical treatment group. A total of 90 patients are planned to be enrolled (52 in the PNS group and 38 in the BMT group). Patients in the intervention group receive a percutaneous implantation of a unilateral or bilateral lead which is externalized for a trial phase for 3–14 days. After trial phase only patients with at least 50% reduction of pain receive an impulse generator for permanent stimulation. Regular visits for participants are planned on day 0, after 3 months (± 30 days), 6 months (± 30 days), and 12 months (± 60 days). The primary outcome measurements is the difference in Numeric Pain Rating Scale (NRS) between baseline and after 6 months. Secondary outcomes is improvement of pain associated disability (ODI) and improvement of health-related quality of life after 6 and 12 months.

**Discussion:**

We have described the protocol for a prospective, multicenter, randomized trial evaluating the influence of PNS on patients with chronic sacroiliac joint syndrome. We believe that PNS on patients with chronic sacroiliac joint syndrome will show promising results regarding pain relief and quality of life in comparison to BMT after 12 months. The design of this trial promises high evidence in comparison to the data to date.

**Trial registration:**

ClinicalTrials.gov, NCT05357300. Registered on April 26, 2022.

### Introduction

#### Background and rationale {6a}

The prevalence of sacroiliac joint pain (SIJP) is estimated to be between 10 and 30% in patients with chronic low back pain, causing up to 4% of total working force loss in Germany [1, 2]. As the socioeconomic impact remains huge, numerous conservative and surgical treatment modalities for SIJP have been described.

Initial management of patients with physiotherapy and best medical treatment is complemented by intra-articular injections, radiofrequency or cryo-ablation of the lateral branches of S1 to S3, and sacroiliac joint fusion. To date, evidence regarding long-term pain relief remains limited [3–7]. Spinal cord stimulation (SCS) is a well-established technique to treat patients with chronic low back pain [8–11]. However, the effect on patients with SIJP is not consistent. Therefore, peripheral nerve stimulation for chronic SIJP was implemented in experimental trials. Clinical data on peripheral nerve stimulation (PNS) for SIJP is still lacking as only limited retrospective data and case reports have been published [1, 12]. Therefore, the authors present a protocol for a prospective, multicenter randomized study to determine the effect of PNS in patients with chronic intractable SIJP.

## Objectives {7}

The primary objective of this study is to evaluate the influence of peripheral nerve stimulation on the pain level, pain-associated disability and quality of life in patients with chronic intractable SIJP with a high evidence level. It is hypothesized that PNS of the rami dorsales (L5–S3) in patients with chronic sacroiliac joint pain is superior compared to the best medical treatment 6 months after therapy.

## Trial design {8}

This is an investigator initiated prospective, randomized, multicenter trial to investigate the influence of peripheral nerve stimulation on patients with chronic sacroiliac joint syndrome. Patients with chronic intractable SIJ pain will be recruited. After informed consent, the patients will be randomized 4:3:PNS group—peripheral nerve stimulation.BMT group—best medical treatment + physiotherapy (current gold standard).

After 6 months, patients from BTM-group with not satisfactory outcome will be offered to switch to the PNS therapy.

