### Outcomes {12}

The primary outcome is the difference in Numeric Pain Rating Scale (NRS) between baseline and after 6 months.

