#### Secondary outcomes

Proportion of patients with ≥ 50% reduction in sacroiliac joint pain (responder) on the NRS (0–100) at 6 and 12 months.Improvement of pain associated disability (ODI) after 6 and 12 months.Improvement of Health-related quality of life after 6 and 12 months.Difference in Numeric Pain Rating Scale (NRS) between baseline and after 12 months.

Clinical relevance and standardization of NRS and ODI has been validated previously. The majority of clinical trials on PNS are monitoring outcomes by NRS and ODI (15–18).

Health economics outcomes:Ability to work, if patients were unable to work because of the chronic back painDoctor visits after inclusion in the study

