## Participant timeline {13}

Participants will participate in the study for 12 months.All patients in the BMT group receive best medical treatment for chronic back pain in the outpatient department and receive physiotherapy treatment for at least 2 months.Patients in the PNS group receive the following procedure:Patients will be prepared for the surgical procedure with blood sample, informed consent and potentially further diagnostic procedures.The surgery will be performed with analgesic sedation or in general anaesthesia:

Percutaneous implantation of the lead (unilateral/bilateral). Connection to extension and externalization

Trial phase for 3–14 days with NRS monitoring.

After trial phase, only patients with at least 50% reduction of pain (NRS) receive the impulse generator gluteal/abdominal for permanent stimulation.

The study schedule is presented in Table 1.

**Table 1 Tab1:** Study schedule

	Screening	V1 (day 1)	V2 (after trial)	V3 (3 months ± 30 days)	V4 (6 months ± 30 days)	V5 (12 months ± 60 days)	Time expenditure (min.)
NRS (0–10) (1 item)	x	x	x	x	x	x	6 × 10 60
ODI (10 items)		x		x	x	x	4 × 20 80
SF-36 (36 items)		x		x	x	x	4 × 30 120
ADS-K		x		x	x	x	4 × 30 120
Patient satisfaction with pain relief (0–10) (1 item)		x		x	x	x	4 × 10 40
PSQI (24 items)		x		x	x	x	4 × 20 80
Neurological status (50 items)		x	x	x	x	x	5 × 30 150
IPG-data (15 items)			x	x	x	x	4 × 30 120

*NRS* Numeric Pain Rating Scale, *ODI* Oswestry Disability Index, *SF-36* The Short Form (36) Health Survey, *ADS-K* General Depression Scale, *PSQI* Pittsburgh Sleep Quality Index, *IPG* implantable pulse generators

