## Statistical methods

### Statistical methods for primary and secondary outcomes {20a}

The primary endpoint will be analysed by mixed linear regression with the change in NRS score from baseline to 6 [12] months as dependent and treatment and baseline value as independent variables. Study center will be added as a random intercept. In order to adjust for relevant covariables, a maximum of four additional variables are included in the model due to the sample size limitations. By this procedure, depending on the correlation of the independent variables with the dependent variable, a gain in power is obtained compared with the calculated sample size [14]. Even in the worst case and a correlation of 0, however, at least the power as specified in the sample size calculation is achieved. As a further analysis to investigate time trends, we will apply a linear mixed effects models as before but consider all time points and include timepoint as an additional, discrete factor. Further, the interaction between treatment and timepoint and a random intercept for the patients will be added.

A chi-square test is used to analyse the proportion of patients with at least a 50% reduction in the NRS value. In a second step, if there are enough patients with a corresponding reduction, a mixed logistic regression model with additional covariates and study center as random intercept is created. The secondary endpoints will be analysed analogously to the primary endpoint. All analyses including *p*-values are to be considered purely exploratory. All results will be reported with 95% CIs.

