## Discussion

We have described our planned protocol for a prospective, multicenter, randomized trial evaluating the influence of PNS on patients with chronic sacroiliac joint syndrome. We believe that PNS on patients with chronic sacroiliac joint syndrome will show promising results regarding pain relief and quality of life in comparison to BMT after 12 months. Clinical data on PNS for SIJP is still lacking and only limited retrospective data, technical notes and case reports have been published. Therefore, our main goal is to generate relevant evidence concerning the effect of PNS on patients with chronic intractable SIJP. The prospective, multicenter design of this trial promises high evidence in comparison to the data to date.

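### Optional PNS for BMT patients after month 6 changes what the 12-month comparison estimates, yet the plan analyses and describes it as PNS versus BMT

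*Protocol article*

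**What the plan says.** - **Switch.** Trial design {8}: "After 6 months, patients from BTM-group with not satisfactory outcome will be offered to switch to the PNS therapy". The article neither defines an unsatisfactory outcome nor gives an expected number of switchers.
- **Follow-up.** Participant timeline {13} keeps participants in the study for 12 months. Nothing says that patients who switch leave follow-up.
- **Endpoints.** The hypothesis in Objectives {7} is set at 6 months, and so is the primary endpoint in Outcomes {12}: "The primary outcome is the difference in Numeric Pain Rating Scale (NRS) between baseline and after 6 months". The secondary outcomes add 12-month versions: "Difference in Numeric Pain Rating Scale (NRS) between baseline and after 12 months", the proportion of patients with at least 50% reduction ("responder) on the NRS (0–100) at 6 and 12 months"), "Improvement of pain associated disability (ODI) after 6 and 12 months", and quality of life at the same two times.
- **Analysis.** Statistical methods {20a} fits a mixed linear regression with treatment and baseline value as independent variables and study centre as random intercept. It then states: "The secondary endpoints will be analysed analogously to the primary endpoint". Responders are compared by a chi-square test. A further mixed model uses all time points with a treatment-by-timepoint interaction. All analyses are called exploratory. Neither {20a} nor the section on non-adherence and missing data {20c} mentions switched patients.
- **Interpretation.** The Discussion expects that PNS "will show promising results regarding pain relief and quality of life in comparison to BMT after 12 months", and the Abstract says the same.

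**The concern.** These statements do not fit together. At month 12 the BMT arm may contain patients treated with PNS, and they are drawn from those who did badly on BMT. Analysed as at month 6, a switched patient who reaches a 50% reduction on PNS counts as a BMT responder. In the all-timepoint model, switching would make the treatment effect appear to shrink between months 6 and 12 even if PNS kept its full effect, and that could be misread as PNS wearing off. The article's rationale is that evidence on long-term pain relief is limited, so readers will look closely at the 12-month results.

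**Working it through.** **Inputs from Sample size {14}:** difference 2.1 points, SD 3, two-sided 5%, power 80%, unpaired t-test, 25% non-responders in the PNS arm, 10% dropout, 52 PNS and 38 BMT patients.

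**Step 1: reproduce the plan's figure.** The t-test calculation with standardised difference 2.1/3 = 0.70 gives 33.02, rounded up to 34 per group. Then 34/0.75 = 45.3, rounded up to 46; 46/0.9 = 51.1, rounded up to 52; 34/0.9 = 37.8, rounded up to 38; and 52 + 38 = 90. The stated sample size reproduces. It applies to the 6-month comparison, and the article sets no power target for 12 months. Power with 34 per group is 81%.

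**Step 2: dilution at 12 months.** Let c be the share of BMT patients who switch. The documents do not give c, so a range is shown. Assume that the between-arm effect of PNS stays at 2.1 points to month 12 and that the SD stays at 3.

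- (a) Every switcher gains the full effect: difference = 2.1 × (1 − c).
- (b) Only 75% of switchers benefit, mirroring the plan's 25% non-responders: difference = 2.1 × (1 − 0.75c).

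| c (assumed) | (a) difference | (a) power, 34 per group | (b) difference | (b) power, 34 per group |
|---|---|---|---|---|
| 0% | 2.10 | 81% | 2.10 | 81% |
| 10% | 1.89 | 73% | 1.94 | 75% |
| 25% | 1.58 | 57% | 1.71 | 64% |
| 50% | 1.05 | 30% | 1.31 | 43% |
| 75% | 0.53 | 11% | 0.92 | 24% |

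With all 52 and 38 patients analysed, power is 90% at c = 0. It is 68% (a) or 75% (b) at c = 25%, and 37% (a) or 53% (b) at c = 50%.

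**Step 3: the time-trend model.** Under (a) with c = 50%, the treatment effect would appear to change by 1.05 − 2.10 = −1.05 points between months 6 and 12, although the effect of PNS was held constant.

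**Step 4: order of V4 and the switch.** Table 1 lists "V4 (6 months ± 30 days" as the window, while Trial design {8} opens the switch after 6 months without naming V4. The article does not state which comes first.

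**The case against.** The best defence has four parts.

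- **The main question is protected.** The hypothesis and primary endpoint are at 6 months, every 12-month endpoint is secondary, and all analyses are called exploratory. This stands and lowers the severity. It does not correct a mislabelled comparison, because estimates with 95% confidence intervals will still be reported.
- **The as-randomised comparison is valid.** It is, for PNS versus BMT with optional later PNS, and it should be kept. The error lies in reading it as PNS versus BMT. A reader might infer that the 12-month analysis itself is invalid, but the documents do not support that.
- **The analysis plan may handle switching.** Detailed rules for switchers can be left to it. The point rests instead on what the article does state: 12-month endpoints analysed like the primary, and a 12-month expectation worded as PNS against BMT. That wording is an expectation in a Discussion, not a planned hypothesis, but it tells readers how to take the result.
- **The size is conjecture.** The article gives no switch rate, so the figures show a range and are not a forecast. A reader might infer a high rate from the preliminary BMT figures: with mean reduction 1.4 and SD 1.7, Φ((3 − 1.4)/1.7) = 0.83 would miss a 50% reduction from the minimum entry score of 6 out of 10. That does not predict switching. It is a normal approximation to preliminary data on 10 patients in all, an unsatisfactory outcome need not mean less than 50% reduction, and being offered surgery is not accepting it.

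**Conclusion.** The concern holds for the 12-month secondary endpoints and the all-timepoint model, at moderate severity. The 12-month contrast by randomised arm estimates PNS versus BMT with optional PNS from month 6. It is probably diluted towards no difference, so a small 12-month difference would not show that PNS had lost its effect. With 25% to 50% switching, the planned difference falls to about 1.6 to 1.05 points if all switchers gain the full effect, or to about 1.7 to 1.3 points if 75% do. These figures rest on an assumed switch rate, a constant PNS effect to month 12, switchers gaining as much as the average PNS patient by V5, and an unchanged SD.

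A reader might also infer from the 30-day window that the primary endpoint is contaminated. The documents do not support that. Judging an outcome unsatisfactory after 6 months presupposes a 6-month assessment, which is V4, and no section allows a switch before it. The primary endpoint is unaffected provided V4 is recorded before any switch; the article should say so.

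**What to change.** The switch offer itself is not changed.

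1. Keep the as-randomised 12-month analysis, label it *PNS versus BMT with optional PNS from month 6*, and reword the 12-month statements in the Abstract and Discussion to match.
2. Record the switch date, and report the number, timing and outcomes of switchers separately.
3. Add a supportive 12-month estimate from the repeated-measures model with post-switch BMT values set to missing. State that it relies on missing at random given the observed 3- and 6-month values. Switchers are selected for poor outcome, so the estimate becomes largely extrapolation if many switch: at 50% switching, only 17 of 34 BMT patients would keep 12-month data.
4. For the primary analysis, use the last NRS recorded before any switch as the 6-month value. Reconcile Trial design {8} with Participant timeline {13} on the order of V4 and the switch.

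The cost is wording in the protocol and analysis plan, one date field in the eCRF, and one extra model fit. No extra patients or visits are needed. The changes should be made before 12-month data are analysed.

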## Methods: participants, interventions and outcomes

### Study setting {9}

Participants will be recruited from outpatient clinics of academic hospitals and community clinics all over Germany. The Charité Coordination Clinical Trial Office (CTO) is helping with study planning and is performing the monitoring and the digital data management of the study. Electronic CRFs were created together with the CTO. Data will be collected according to the study schedule. List of study sites can be obtained at CTO.

### Eligibility criteria {10}

#### Inclusion criteria

Patients with chronic sacroiliac joint pain refractory to conservative treatment.Patients with a Numeric Rating Scale (NRS) score of at least 60/100.Patients with temporary pain reduction of at least 50% (NRS) after fluoroscopy guided SIJ infiltrationPatients received conservative treatment for at least 6 months including physiotherapy and pain medication.Patients which from a medical point of view have enough cognitive capacities to understand the programming of Implantable Pulse Generators (IPGs).

#### Exclusion criteria

Patient’s age < 18 years.Pregnancy.Acute traumatic injury of the SIJ.Active inflammation or neoplastic infiltration of the SIJ.Neoplastic diseases of the spine.Neoplastic diseases of the spine.Spinal surgery within the last 6 months.The SIJ pain is not the leading symptom.  Contraindication for neuromodulation device (severe psychiatric disease, severe coagulation disorder, acute infection, active autoimmune disease with immunosuppression).

All participating centers require spinal imaging and blood samples as a standard prior to treatment of SIJP to rule out other pathologies as cause of the pain.

### Who will take informed consent? {26a}

Written informed consent from potential trial participants will be obtained from the investigators at each clinic. As potential participants are seen in specialized neuromodulation outpatient clinics, patients meeting eligibility criteria are informed in person by clinicians and provided information material.

### Additional consent provisions for collection and use of participant data and biological specimens {26b}

Biological specimens will not be collected by this trial and therefore not stored or used for research. All data collection processes are provided by the informed consent form. Collected data will be de-identified and not used for other purpose.

## Interventions

### Explanation for the choice of comparators {6b}

Since evidence regarding long-term pain relief with the different treatment modalities such as intra-articular injections, radiofrequency ablation, cryoablation and sacroiliac joint fusion is limited, the gold standard remains best medical treatment (BMT) combined with physiotherapy. Therefore, this trial compares outcomes of PNS of the rami dorsales (L5–S3) to outcomes of BMT and physiotherapy. BMT will be performed at a specialized outpatient clinic to ensure high quality level of treatment. On top of that, physiotherapy has to be done continuously for at least 2 months during this period. Patient will receive the prescription from the study centers to ensure implementation.

### Intervention description {11a}

The operative technique of PNS of the rami dorsales L5–S3 has been described previously [1]. Surgery can be performed in local anaesthesia with additional sedation or in general anaesthesia. Patients are placed in prone position with the head lying in a soft head shell or pillow. The sacroiliac joint is marked on both sides and the skin is disinfected with Octeniderm (Schülke & Mayr GmbH, Norderstedt, Germany) in usual fashion. The skin and the periost of the sacrum medial to the SIJ is infiltrated with 5–10 ml of 1% lidocaine, if patients did not receive general anaesthesia. After 2-cm skin incision and subcutaneous preparation, a 14-gauge hollow hypodermic needle (Entrada™, Needle, Boston Scientific, MA, USA) is placed along the sacrum lateral to the dorsal foramen and medial to the SIJ with under fluoroscopic guidance and the stylet is removed. The percutaneous PNS lead (8-contact, Linear™ 3–6 lead, Boston Scientific, MA, USA) is inserted through the needle and positioned between the sacroiliac joint and the sacral foramina as close to the sacral surface as possible with contacts stimulation the rami dorsales S1-S3 (Fig. 1). To verify optimal placement, a lateral fluoroscopic scan is performed (Fig. 2). The lead is fixed with an anchor (BostonScientific, MA, USA) and can be tunneled to a separately prepared subcutaneous gluteal pocket. Here it will be connected to an extension lead, which will be tunneled through the skin to enable external stimulation.

**Fig. 1 Fig1:**
[figure not shown]
Postoperative coronar X-rays of two different patients with placement of the leads between the sacroiliac joint and the sacral foramina. Note that the Implantable Pulse Generator in the gluteal pocket is displayed on the right

**Fig. 2 Fig2:**
[figure not shown]
Postoperative sagittal X-rays of two different patients with placement of the leads close to the sacral surface. **A** Patient with unilateral lead. **B** Patient with bilateral leads

The part of the extension lead protruding the skin is sutured sturdily and connected to the external stimulator. After successful trial phase of 3–14 days patients with at least 50% pain reduction in NRS score, patients receive the implantation of the impulse generator (WaveWriter Alpha™, Boston Scientific, MA, USA), which will be connected to the stimulation lead for permanent stimulation. The extension will be discarded. Therefore, the extension lead is cut close to the skin and removed. The impulse generator is then inserted subcutaneously into the initially prepared subcutaneous pocket. Therefore, the skin incision is widened to a 5–6-cm skin incision, the impulse generator is fixed with a suture and the generator is connected to the lead.

If patients did not experience a 50% pain relief, the leads will be explanted.

### Criteria for discontinuing or modifying allocated interventions {11b}

As study participation is voluntary, all participants may withdraw from the study at any time. Patients randomized to the PNS group can have their PNS system explanted at any time if they want to withdraw from the study. The study team will not collect any further data from participants who withdraw. Data already collected will be retained, as agreed in written informed consent. After withdrawal from the study, participants will not be allowed to enter back into the study at a later date.

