### Plans to promote participant retention and complete follow-up {18b}

The study group will contact participants by mail and phone throughout the trial and arrange all appointments with participation in this study. The reported scope of 30–60 days in the 3-, 6- and 12-month outpatient visits gives more flexibility to the participants. The importance of the visits is explained to participants in advance. Participants have the opportunity to contact the study nurse at any time for questions concerning follow-up. If participants want to withdraw from the study, a final outpatient visit is scheduled in order to complete data collection.

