### Data management {19}

All data are stored in an encrypted form in the REDCap (Research Electronic Data Capture) database. IPG data are recorded by the technical assistants and transferred to the same database. Password protection ensures that only authorized persons from the study have access to participants data. Data collection will be done in the outpatient visits, so that there will be no need for questionnaires by post or mail.

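### Neither withdrawal rule secures the 6-month NRS, and tying on-request explantation to leaving the study risks arm-dependent, informative loss of the primary outcome

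*Protocol article*

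**What the plan says.** All references are to the protocol article.

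- **Discontinuation, {11b}.** On data after withdrawal: "The study team will not collect any further data from participants who withdraw". On stopping the device: "Patients randomized to the PNS group can have their PNS system explanted at any time if they want to withdraw from the study". On return: "After withdrawal from the study, participants will not be allowed to enter back into the study at a later date". The section describes no arrangement for a patient who wants stimulation stopped but is willing to keep attending visits.
- **Retention, {18b}.** "If participants want to withdraw from the study, a final outpatient visit is scheduled in order to complete data collection".
- **Intervention description, {11a}** (text after the Fig. 2 caption). There is a second route to explantation, after the trial phase: "If patients did not experience a 50% pain relief, the leads will be explanted". Whether these patients continue in follow-up is not stated.
- **Outcomes, {12}.** The primary outcome is the NRS change from baseline to 6 months. Table 1 sets that visit (V4) at 6 months ± 30 days.
- **Sample size, {14}.** The PNS arm alone is enlarged for 25% non-responders. Both arms are then enlarged for 10% dropout, giving 52 + 38 = 90.
- **Missing data, {20c}.** A home visit is offered to patients who cannot attend, and missing a whole visit does not make a patient a dropout.

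**The concern.** The section that should govern stopping the allocated treatment deals only with leaving the study. A site reading it may treat a request for explantation as a withdrawal, and {11b} then ends data collection. Sections {11b} and {18b} also give a site different instructions on what to collect from someone who is leaving.

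The loss need not fall evenly. Only PNS patients have a device to remove, and a request to remove it will often follow poor relief or a complication. A BMT patient who is doing badly has a reason to stay, because Trial design {8} offers a switch to PNS after 6 months. If the PNS patients who leave are those with little benefit, the remaining PNS patients look better than the arm as randomised, and the trial is open-label with a patient-reported primary outcome. An analysis plan can model such gaps, but it cannot recover values that the protocol told sites not to collect.

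**Working it through.** **1. The plan's own figure.** Inputs from Sample size {14}: mean NRS reduction 3.5 (PNS) and 1.4 (BMT), difference 2.1, planning SD 3, two-sided 5%, power 80%, unpaired t-test.

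- Noncentral t: power is 0.7997 at 33 per group and 0.8116 at 34, so n = 34.
- PNS: 34 / 0.75 = 45.3, rounded up to 46; then 46 / 0.90 = 51.1, rounded up to 52.
- BMT: 34 / 0.90 = 37.8, rounded up to 38.
- Total 52 + 38 = 90. The figure reproduces.

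Dividing by 0.75 is the adjustment for patients who contribute no outcome. The calculation therefore treats the 25% as non-contributors, although no section says that they leave follow-up.

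**2. What each rule yields for a patient who leaves before month 6.**

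- {11b}: nothing after withdrawal, and re-entry is barred.
- {18b}: one value at the time of leaving. It serves as the 6-month value only if it happens to fall inside the V4 window.
- {20c}: home visits help patients who cannot travel. Nothing there extends them to patients who have withdrawn.

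**3. What could be at stake.** The documents give no withdrawal rate by arm and no outcomes for lost patients. Assumptions: lost PNS patients have a true 6-month reduction x between 0 and 1.4 (the BMT mean); BMT stays at 1.4; lost patients are left out of the 6-month comparison. Two readings of the 3.5 are possible.

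*Reading A: 3.5 is the mean of retained PNS patients, and the 25% are lost.* The as-randomised PNS mean is 0.75 × 3.5 + 0.25x.

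- x = 0: mean 2.625, difference 2.625 − 1.4 = 1.225, overstatement 2.1 − 1.225 = 0.875.
- x = 1.4: mean 2.975, difference 1.575, overstatement 0.525.

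*Reading B: 3.5 is the mean of all PNS patients, and a fraction w is lost.* The retained mean is (3.5 − wx) / (1 − w), and the overstatement is that mean minus 3.5.

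- w = 0.05: x = 1.4 gives 3.61 (overstatement 0.11); x = 0 gives 3.68 (0.18).
- w = 0.10: x = 1.4 gives 3.73 (0.23); x = 0 gives 3.89 (0.39).

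Under A the overstatement is about 0.5 to 0.9 points; under B it is about 0.1 to 0.4. Under A an observed 2.1 would pass the 2-point difference that {14} cites as clinically meaningful, while the as-randomised difference of 1.2 to 1.6 would not.

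**The case against.** **The two withdrawal sections can be read in sequence.** {18b} concerns people who want to leave and {11b} those who have left: a closing visit, then nothing more. That is a fair reading. It would remove the conflict, but a site should not have to work it out, and it still does not supply a 6-month value.

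**The explantation sentence does not say that explanted patients leave.** It lets patients who withdraw have the system removed, and {11a} does not link a failed trial phase to withdrawal. This stands. What remains is that {11b} ties its only on-request route to leaving and gives no alternative. The full protocol may do so, but the wording shown needs correcting.

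**Withdrawal is open to both arms.** "As study participation is voluntary, all participants may withdraw from the study at any time". The only loss rate given, 10% dropout, applies to both arms. Other procedures for the joint are barred in both ({11d}), so dissatisfied BMT patients may leave too. A reader might infer that the 6-month NRS will be lost mainly from PNS patients who did badly. That is plausible, but no figure in the document shows it.

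**A large bias is not established.** A reader might combine the inflation steps into 18 of 52 PNS patients missing (35%) against 4 of 38 BMT (about 10%), give the 18 no improvement, and obtain 34 × 3.5 / 52 = 2.29 and a difference of 0.89. The documents do not support this. Thirteen of the 18 (0.25 × 52) are trial-phase failures, whom no section classes as withdrawn. Zero change is an extreme value, applied there to one arm only. Applying it to the BMT dropouts as well gives 34 × 1.4 / 38 = 1.25 and a difference of 1.04.

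**Collection is not confined to the clinic.** Data management {19} says "Data collection will be done in the outpatient visits, so that there will be no need for questionnaires by post or mail", but {20c} offers home visits. A telephone NRS is therefore an optional extra and not a missing safeguard.

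**Conclusion.** The point holds as a risk created by the wording. {11b} and {18b} need reconciling. Neither secures the 6-month NRS of someone who leaves early, and {11b} provides no way to stop stimulation on request and remain in follow-up. Because explantation belongs to one arm, and {14} already counts that arm's 25% non-responders as non-contributors, the loss could depend on both arm and outcome.

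The size is an assumption and not a document figure: about 0.5 to 0.9 NRS points under reading A and about 0.1 to 0.4 under reading B. Both ranges rest on true changes of 0 to 1.4 in the lost patients, an unaffected BMT mean, and an analysis that omits the lost patients. Every scenario computed favours PNS, but loss of poor outcomes from BMT would offset it. This is a cheap improvement to make while recruitment is open, because missed 6-month values cannot be collected later.

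**What to change.** - Reconcile {11b} and {18b} so that one rule states what is collected when a patient leaves.
- State that stopping or explanting the device, or stopping BMT, is not in itself study withdrawal. This concerns data collection only and changes no treatment rule.
- Ask every randomised patient, including those who fail the trial phase, for the V3, V4 and V5 outcomes unless they withdraw consent to further data collection. Analyse them in the arm to which they were randomised.
- Record the date and reason of each withdrawal, and separately of each explantation.
- Optionally, accept the single NRS item by telephone within the V4 window when neither a clinic nor a home visit is possible. Some values would then come from a different mode of collection.

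The cost is revised protocol and consent wording and some added follow-up effort. One consequence should be faced openly. If reading A is right, the as-randomised difference is 1.2 to 1.6 points, and power with 46 against 34 patients at SD 3 is 43% to 63%. Full follow-up would reveal that dilution; it would not cause it.
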